## Methods

### Design and setting

The study is a randomized controlled trial (RCT) with a 2 × 2 factorial design. This design allows to test the main effects of the e-Health and PA separately, as well as their combined effect on lasting RTW. The study includes a baseline assessment and 3 follow-up assessments at 3 months (after e-Health), 6 months (after PA) and 12 months. Afterwards a process evaluation will be conducted following the Steckler and Linnan framework [16, 17], including a realist evaluation [18]. The process evaluation aims to provide insights in what elements of the stepped-care approach work, for whom and under which circumstances and to evaluate to what degree the implementation of the stepped-care approach was conducted as intended.

The study will be carried out in a large Dutch occupational health service (OHS) organization. The OHS consists of about 4,000 employees – mainly white-collar workers. Occupational health (OH) practitioners from the OHS organization, which has multiple branches spread over the Netherlands, are involved in this study. The core business of the OHS is to offer services to different organizations with the goal to increase the health of workers, promote sustainable employability, prevent sick leave, and offer support for RTW after sickness absence. The task of the OP in the Netherlands is to prevent work-related diseases and to support workability and RTW after sickness absence. The OH practitioner collaborates with the OP and works in task delegation of the OP to reduce the work pressure of the OP. Both OPs and OH practitioners have consultations with employees to promote workplace health, to prevent sickness absence, or to support RTW. Participants will be recruited within the OHS organization itself and their partners.

The trial has been approved by the Medical Ethics Committee of the Amsterdam Academic Medical Center (2023.0474) and is registered in the ISRCTN registry (ISRCTN90663076). Signed informed consents will be obtained from each participant.

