#### e-Health intervention

The e-Health intervention is based on the original Return@Work intervention [11], and adjusted according to the guidelines for common mental disorders of the Netherlands Society of Occupational Medicine [22]. After completing the baseline assessment, employees allocated to the e-Health group will receive access to the e-Health app. The employee is provided with a personal log-in code for the app. The e-Health application starts with an introduction on how to use the app and asks for the necessary permissions of the employee. Following this, the employee answers two navigating questions. The first navigating question is whether or not the employee believes he/she can return to work despite symptoms (cognition of RTW). If this question is followed by a negative answer (i.e. maybe/probably not/no/don’t know), this will be taken as an indication of a negative cognition towards RTW – and the program will include extra exercises to create and reinforce a positive cognition towards RTW. The second navigating question is if the employee labels his/her complaints as more “psychological” or more “physical”. In certain cases, employees with psychological distress categorize their complaints as primarily physical rather than psychological. In such cases, using psychological terminology usually doesn’t resonate with that employee’s experience which can lead to a lower adherence to the program. Therefore, if the employee labels their complaints as more physical, the information that is provided in each module will also be in terms of physical complaints.

Based on the scores of the 4DSQ and the navigating questions, the employee receives specific modules tailored to their needs.

The e-Health app includes the following modules:

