### Outcome measures

#### Effect evaluation

The primary outcome measure is time to lasting RTW. Lasting RTW is defined as RTW to the employee’s previous position, or another position with equal earnings, for a minimum of four consecutive weeks. Time between the first day of absenteeism with psychological distress and lasting RTW is calculated in calendar days and will be based on self-report through monthly diaries that participants are asked to fill in online. In addition, permission was requested to obtain these data from the OHS.

The secondary outcome measures consist of (1) (severity of) stress-related symptoms, (2) total sick-leave days, (3) self-efficacy and (4) self-reported health. Stress-related symptoms are measured with the 4DSQ [19, 24]. This questionnaire consists of 50 items, with subscales distress, depression, anxiety, and somatization. The items are scored on occurrence in the past week on a 5-point Likert scale, ranging from “no complaints” to “very often/continuously”. The total number of sick-leave days is based on the same data as time to lasting RTW (self-report and/or absenteeism record). Self-efficacy with regard to RTW is measured using the Work Self-Efficacy questionnaire. This questionnaire consists of 11 items and is specifically designed to measure self-efficacy for RTW in employees with mental health problems [25]. Self-reported health is measured with the Patient Reported Outcomes Measurement Information System (PROMIS) questionnaire. The PROMIS covers three domains of reported health: physical, psychological and social aspects of wellbeing. [26].

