#### Covariates

By means of questionnaires we will gather information on the following covariates: (1) sociodemographic data, (2) job characteristics, (3) psychosocial risk-factors, (4) behavioral determinants of RTW. Sociodemographic data will include age, sex as reported by the employee, educational level and household composition. Job characteristics include type of work and contractual hours. Psychosocial risk-factors will be measured using the Job Content Questionnaire (JCQ; [27]. This questionnaire is designed to measure the social and psychological characteristics of jobs, including psychological demands, decision latitude (the employees’ potential control over his tasks and conduct during the workday), social support, physical demands and job insecurity. Behavioral determinants of RTW following the ASE model consist of the employees’ attitude, social influence and self-efficacy [28, 29].

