#### Data analysis

Descriptive statistics will be provided for all relevant variables at baseline. To investigate the effectiveness of the interventions of the stepped care approach on lasting RTW a cox-regression will be conducted. To determine the effect of e-Health separately, the group who received [e-Health and PA] will be combined with the [e-Health only] group, and compared to the control- and [PA only] group. The same logic applies to PA; the PA groups will be combined and compared to the control- and [e-Health only] group. To test whether the combination of e-Health and PA in a stepped-care approach is superior to the separate interventions alone, we will study the interaction between PA and e-Health. For the secondary outcomes, depending on the type of outcome measure (continuous/categorical) generalized linear models or mixed effects logistic regression will be used. Analyses are conducted both unadjusted and adjusted for potential confounders. Additionally, effect modification of several factors, such as the (severity of) stress-related symptoms and cognition towards RTW despite symptoms, will be investigated by using interaction terms.

All analyses will be performed according to the intention-to-treat principle (ITT), which implies that all employees are analyzed according to the group they were assigned to, regardless of whether they actually received the intervention.

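### For the 4DSQ and PROMIS scores, the article does not place the outcome's own baseline value in either described analysis, nor say which analysis is the main one, so available precision may be lost

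*Protocol article*

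**What the plan says.** The secondary outcomes in the Effect evaluation section are "1) (severity of) stress-related symptoms, (2) total sick-leave days, (3) self-efficacy and (4) self-reported health". Three of the four are questionnaire scores: the 4DSQ subscales, RTW self-efficacy and PROMIS. On timing, Design and setting says: "The study includes a baseline assessment and 3 follow-up assessments at 3 months (after e-Health), 6 months (after PA) and 12 months".

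For these outcomes the Data analysis section states that, depending on whether the outcome is continuous or categorical, "generalized linear models or mixed effects logistic regression will be used". It then adds: "Analyses are conducted both unadjusted and adjusted for potential confounders". The confounders are not named, and neither analysis is designated as the main one.

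The Covariates section lists "1) sociodemographic data, (2) job characteristics, (3) psychosocial risk-factors, (4) behavioral determinants of RTW". The last group consists of "attitude, social influence and self-efficacy". Baseline 4DSQ and PROMIS are not in the list.

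Symptom severity enters a model elsewhere only in the additional interaction analyses: "effect modification of several factors, such as the (severity of) stress-related symptoms and cognition towards RTW despite symptoms, will be investigated". Otherwise, Data analysis mentions baseline variables only for descriptive statistics.

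**The concern.** In a randomised trial a covariate earns its place by predicting the outcome, because randomisation already removes confounding in expectation. For a repeated questionnaire score, the obvious predictor is the same score at baseline. Selecting variables as confounders does not lead reliably to that one, and it leaves room to choose the set after the data are seen.

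The baseline information should be at hand. The e-Health section shows that 4DSQ scores exist by the time the app starts: "Based on the scores of the 4DSQ and the navigating questions, the employee receives specific modules tailored to their needs". Entry requires a positive distress screener, so baseline severity can vary, and the Randomization section describes no stratification by severity.

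Two things are at stake. One is efficiency, in a trial sized for time to RTW with no power target for the scores. The other is how the result in hand is read: if the groups differ by chance in baseline symptoms, part of that difference persists in an unadjusted follow-up comparison. Since neither analysis is named as the main one, the less efficient could become the headline result.

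**Working it through.** **Inputs from the article (Sample size section).** 144 participants, 36 per group, power 80%. Each factorial main effect pools two groups, so 2 × 36 = 72 are compared with 72.

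**The plan's own figure.** 144 was derived for time to RTW with a hazard ratio of 1.8; no figure is given for the scores. At two-sided 0.05 and 80% power, that hazard ratio needs 91 events (Schoenfeld) or 97 (Freedman). Then 144 participants would imply that 91/144 = 63% or 97/144 = 67% reach lasting RTW. The article states no such rate, so 144 can be neither confirmed nor refuted. It is used here only as the number analysed.

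**Assumptions.**
- rho is not given, so 0.3, 0.5 and 0.7 are shown.
- The test is two-sided at 0.05. The article prints an alpha of 0.5, which is a separate matter.
- The score has equal SD in both groups, and the unadjusted analysis compares follow-up scores at one visit.

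**Formulas, in SD units.**
- SE without baseline = √(2/72) = 0.167.
- SE with own baseline = 0.167 × √(1 − rho²).
- Detectable difference at 80% power = (1.960 + 0.842) × SE.
- Power for a true 0.4 SD difference = Φ(0.4/SE − 1.960).
- Participants needed without baseline for the same precision = 144/(1 − rho²).
- Shift in the unadjusted estimate from a chance baseline difference D = rho × D.

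| | No baseline | rho 0.3 | rho 0.5 | rho 0.7 |
|---|---|---|---|---|
| SE | 0.167 | 0.159 | 0.144 | 0.119 |
| Reduction in SE | – | 4.6% | 13.4% | 28.6% |
| Detectable difference | 0.467 | 0.445 | 0.404 | 0.333 |
| Power for 0.4 SD | 67% | 71% | 79% | 92% |
| Participants needed without baseline | – | 158 | 192 | 282 |
| Shift in unadjusted estimate if D = 0.2 SD | – | 0.06 | 0.10 | 0.14 |

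**How large D could be.** Its 95% chance range is ±1.96 × 0.167 = ±0.33 SD, so 0.2 SD is not extreme.

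**Simulation check (20,000 trials per rho, no true effect).** Both estimators averaged zero. The slope of the unadjusted estimate on the baseline difference was 0.30, 0.50 and 0.70; with the baseline covariate it was about zero. The empirical SDs agreed with the table: 0.167, 0.166 and 0.166 unadjusted, against 0.160, 0.144 and 0.119 adjusted.

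**The case against.** The strongest reply is that silence is not exclusion. The confounders are not enumerated, and the Covariates section does not call its list the adjustment set or say that it is complete. The scores were already introduced as outcomes, so their absence from a list of further variables shows little. The planned interaction models for symptom severity would normally contain a severity main effect too. A journal article also commonly leaves exact covariates to a fuller protocol or SAP. This stands against the inference that the plan leaves the baseline score out of both analyses: the article does not say so. What remains is the adjustment principle that it does print, and the missing choice of main analysis.

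A second reply is that an analysis called unadjusted could still use baseline, as a change score or as part of a repeated-measures outcome. That is possible but not stated. For continuous scores the article names generalized linear models, mixed effects are named only for logistic regression, and no change score is mentioned. A change score would not close the gap either: its SE is 0.167 × √(2(1 − rho)) = 0.197, 0.167 and 0.129 at rho 0.3, 0.5 and 0.7, above the covariate-adjusted SE each time.

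Third, a reader might infer that the unadjusted comparison is biased. It is not: it is unbiased over randomisations, and its standard error already allows for chance imbalance, so the type I error rate is kept.

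Fourth, the gain is small at low rho: 4 power points at rho 0.3 for a 0.4 SD effect. The table also compares against the purely unadjusted model; if the listed covariates predict the outcome, the gain over the promised adjusted analysis would be smaller. Both points stand.

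**Conclusion.** The point holds for the 4DSQ subscales and PROMIS. As printed, the plan does not provide for adjustment by the outcome's own baseline score, describes adjustment as confounder control, and leaves open which analysis leads. The cost is precision, plus error conditional on the imbalance that happens to arise. At 72 versus 72 the standard error would be about 5%, 13% or 29% smaller with the baseline score at rho 0.3, 0.5 or 0.7. These sizes rest on the assumed rho and on the unadjusted analysis being a comparison of follow-up scores.

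Extending the criticism in full to RTW self-efficacy would go too far. Self-efficacy is among the listed covariates; the article just does not say whether it is measured there with the outcome instrument. The outcomes concerned are secondary, so the change is advisable and does not touch the primary analysis.

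**What to change.** In Data analysis, or in the SAP, state that:

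- the main model for each 4DSQ subscale, for PROMIS and, for consistency, for RTW self-efficacy includes that score's own baseline value as a covariate, with a baseline-by-visit term if visits are modelled jointly;
- any further covariates are prespecified because they are prognostic, and are not chosen as confounders;
- the purely unadjusted comparison is reported as supplementary.

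The cost is a few lines of text, one degree of freedom per model (more if baseline-by-visit terms are used), and a rule for a missing baseline score. No extra participants or visits are needed. The text does not itemise the baseline questionnaires, so confirm that PROMIS and the self-efficacy outcome instrument are among them.

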#### Process evaluation

A process evaluation will be conducted based on the Steckler and Linnan framework [16, 17], including a realist evaluation [18]. The goal of the process evaluation is to identify underlying mechanisms that lead to success or failure of (parts of) the stepped-care approach. Depending on the effectiveness of the stepped-care approach, it will be used to answer questions about “what works, for whom, in what contexts in what respects and how” [30]. The process evaluation consists of two components: a realist evaluation and the evaluation that follows the guide of Saunders et al. [17] – which is based on the Steckler and Linnan framework. Typically, a realist evaluation is expressed in the form of context-mechanism-outcome (CMO) configurations. These configurations will be formed by gathering information about the experience with the stepped-care approach using mixed methods, after the intervention took place [31]. For example, a participant who received the stepped-care approach will be interviewed on what elements did/didn’t work – and why they think that was the case. This information is then used to form CMO’s for that participant.

For the second part of the process evaluation we will follow the guide by Saunders et al. [17] to investigate the implementation of the stepped-care approach. This evaluation will consist of six key components: fidelity, dose delivered, dose received in terms of exposure, dose received in terms of satisfaction, reach, recruitment and context.

*Fidelity* refers to the extent to which the stepped-care approach was implemented according to the pre-specified plan.*Dose delivered* relates to the degree which employees who were supposed to receive the stepped-care approach (or one of its elements) actually received those.*Dose received in terms of exposure* refers to the extent to which employees actively engaged in the (the different components of the) stepped-care approach.*Dose received in terms of satisfaction* refer to the satisfaction with the stepped-care approach of all stakeholders (employees, employer and OH practitioner).*Reach* considers the degree to which employees on sickness absence with psychological distress participate in the intervention.*Recruitment* concerns the procedures of how the employees are recruited, and the reasons for not participating in the study.*Context* refers to the environmental or organizational factors that may impede or facilitate the intervention implementation.

For both components of the process evaluation, data will be gathered using mixed methods. At approximately 6 months (T2), when the stepped-care approach is finished, employees in one of the three experimental conditions (e-Health and PA, e-Health only, PA only) will receive additional questions to measure their experience with the stepped-care approach and the separate elements. In addition, semi-structured interviews will be held separately with 8 to 10 employees, 5 supervisors, the two RTW-coordinators and 3 to 5 OPs. The interviews will be audio-recorded and transcribed verbatim, coding and analyses will be performed using MAXQDA software. Further, quantitative information from the app including app usage data, attendance logs will be collected and analyzed, as well as the information from the forms concerning the PA.

## Discussion

In the RESTART study, we will evaluate the effectiveness of a stepped-care approach on lasting RTW for employees on sickness absence with psychological distress. We will examine the main effects as well as the combined effect of the e-Health and PA on time to lasting RTW. We hypothesize that the stepped-care approach, e-Health followed by PA, will be more effective on time to lasting RTW compared with usual care, and e-Health or PA only.

As has been shown in previous research, there are three identified key elements for successful lasting RTW for employees with psychological distress. These include an explicit focus on RTW and not only on reduction of symptoms, having a positive cognition towards RTW and involvement of the workplace environment [11, 12]. In the RESTART study, we combine these three elements in a new stepped-care approach. The first step – the e-Health program – aims to develop and reinforce a positive cognition towards RTW through different modules tailored to the employee’s needs. With persistent sickness absence the program is followed by the second step – the PA – involving the workplace environment in a more substantial manner. Since the PA has shown to be more effective for employees with a positive cognition towards RTW and the aim of the e-Health program is to develop and reinforce such a positive cognition, the two interventions in the stepped-care approach complement each other.

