### Randomization and blinding

Randomization takes place on employee level. In addition to usual care, participants can receive e-Health and/or PA. This leads to a 2 × 2 factorial design, which allows to test the main effects of e-Health and PA separately, as well as the combined effect on lasting RTW. Therefore, participants are randomized twice, which results in two comparisons in the main outcome analysis: PA vs. not PA and e-Health vs. no e-Health. On top of usual care participants receive either: (1) e-Health and PA, (2) e-Health only, or (3) PA only (see Fig. 1). A time schedule of enrolment, interventions, and assessments are presented in Fig. 2. Both randomizations take place directly after baseline to ensure even-sized groups. If, however, participants who are assigned to receiving PA (partially) returned to work before PA starts, they will not receive PA.

A computer-based randomization list, generated by an independent researcher, will be used to allocate participants, based on their participant-ID, to one of the four groups. Before the statistical analyses are performed the condition-IDs are recoded by an independent researcher, which allows the primary researcher to be blinded for the allocation and the RCT to be single-blind.

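### The hypothesis that stepped care beats usual care has no stated contrast, and the pooled comparisons do not show what either intervention does alone if the two reinforce each other as expected

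*Protocol article*

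**What the plan says.** **Hypothesis.** The Discussion of the protocol article says: "We hypothesize that the stepped-care approach, e-Health followed by PA, will be more effective on time to lasting RTW compared with usual care". The same sentence goes on to claim superiority over each intervention given alone.

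**Main comparisons.** Randomization and blinding says that randomising twice leads to "two comparisons in the main outcome analysis: PA vs. not PA and e-Health vs. no e-Health".

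**Definition of those comparisons.** Data analysis builds each one by pooling arms. For the app: "To determine the effect of e-Health separately, the group who received [e-Health and PA] will be combined with the [e-Health only] group". The reference group for this is usual care merged with the arm assigned PA without the app. For the Participatory Approach (PA): "the PA groups will be combined and compared to the control- and [e-Health only] group".

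**The combination.** Its one planned analysis is the interaction between the two factors, with this purpose: "To test whether the combination of e-Health and PA in a stepped-care approach is superior to the separate interventions alone". Usual care is not mentioned there. Design and setting, Randomization and blinding, the Discussion and its Strengths and limitation section all name a combined effect as a target, but none gives it another contrast.

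**Expected relation between the interventions.** The Background reports that PA helped only employees with a positive view of returning despite symptoms. The Discussion says the app is meant to build that view, and concludes that "the two interventions in the stepped-care approach complement each other".

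**The concern.** There are two linked problems.

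First, the lead hypothesis and the listed analyses do not meet. In neither main comparison is the reference group usual care: half of each reference group is assigned the other intervention. Nor does the interaction test stand in for the missing contrast. A non-significant interaction would not show that stepped care fails against usual care, and a significant one would not by itself show that it succeeds. Followed to the letter, the plan never tests the claim the trial is presented as testing, although both arms needed are randomised. A contrast added after the data are seen would carry less weight.

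Second, the pooled app comparison is described as giving the app's effect separately. A pooled HR equals the effect of the app without PA only if there is no interaction, and the authors' rationale predicts one. A favourable pooled result could then be used to support offering the app without PA, which the comparison does not address.

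**Working it through.** **1. What each analysis estimates.** Let the log hazard of lasting return to work, relative to usual care, be b1 (e-Health only), b2 (PA only) and b1 + b2 + b12 (both), where b12 is the interaction.

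| Quantity | Log HR | Planned? |
|---|---|---|
| e-Health, pooled over PA | about b1 + b12/2 | yes |
| PA, pooled over e-Health | about b2 + b12/2 | yes |
| Interaction | b12 | yes |
| Combined vs usual care | b1 + b2 + b12 | not stated |
| e-Health only vs usual care | b1 | not stated |
| PA only vs usual care | b2 | not stated |

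The hypothesis about usual care is the fourth row. No planned row equals it, but a Cox model containing b1, b2 and b12 gives it as their sum.

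**2. Pooled effect against effect alone.** Take b1 = b2 = 0 and a combined HR of 1.8. The pooled HR is about exp(ln 1.8 / 2) = √1.8 = 1.34, while each intervention alone has HR 1.0. With 1.3 for each alone and an interaction ratio of 1.5, the pooled HR is about 1.3 × √1.5 = 1.59, against 1.3 alone and 1.3 × 1.3 × 1.5 = 2.54 for combined against usual care.

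**3. Size in a trial of this size.** Simulation inputs:
- From the article: 36 per arm (Sample size); 12 months of follow-up; PA starting six weeks after baseline among those still absent (Participatory approach; Randomization and blinding).
- Assumed: exponential times; a usual-care median of 120 days (the Background gives 120 days for usual care, but in a subgroup of an earlier trial); two-sided 5%; HR 1.0 for each intervention alone; combined HR 1.8 or 2.5. The value 1.8 is the article's design HR; 2.5 is illustrative.

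| Combined HR | PA acts from | Pooled e-Health HR | Significant |
|---|---|---|---|
| 1.8 | six weeks | about 1.2 | about 20% |
| 2.5 | six weeks | about 1.35 | about 38% |
| 1.8 | day 0 | about 1.3 | about 32% |
| 2.5 | day 0 | about 1.45 | about 55% |

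The true HR for e-Health only against usual care is 1.0 in every row, and that direct comparison is significant in about 5% of trials. With PA also in the model, the six-week rows rise to about 24% and 48%. Each scenario used at least 300 simulated trials, so the Monte Carlo standard error is at most √(0.5 × 0.5 / 300), about 3 percentage points.

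**4. Power of the missing contrast.** The article plans 144 participants at HR 1.8 and 80% power. Taking alpha as two-sided 0.05 (an assumption; Sample size prints 0.5), the Schoenfeld formula gives 4 × (1.960 + 0.842)² / (ln 1.8)² = 91 events, or 91/144 = 63% of participants. The article states no event share, so 144 can be neither confirmed nor refuted, and a range is shown.

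Power = Φ(√D/2 × ln HR − 1.96). D is all events for a pooled comparison and half of them for a contrast of two arms.

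| Event share | Pooled, HR 1.8 | Two arms, HR 1.8 | Two arms, HR 3.24 |
|---|---|---|---|
| 63% | 80% | 51% | 98% |
| 80% | 88% | 61% | 99% |
| 100% | 94% | 70% | about 100% |

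Example, 63% share, two arms: D = 45.5, √45.5/2 = 3.373, × 0.588 = 1.98, − 1.96 = 0.02, so power is 51%. HR 3.24 is 1.8 × 1.8, the combined effect if both interventions reach the design HR without interaction.

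**The case against.** The strongest reply is that this is a gap in wording. The article names a combined effect as a target several times and plans an interaction. If the Cox model holds both main effects and the interaction, as is usual, combined against usual care follows from it. Analysis at the margins is also the standard primary analysis of a 2 × 2 factorial trial. The article says which arms are pooled, elsewhere calls the results main effects, and plans the interaction that would qualify them. Naming contrasts is often left to an analysis plan.

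Most of this stands as a limit on the point. A reader might infer that the trial cannot estimate its lead question; it can, from data already planned. A reader might also infer that the article presents the pooled results as effects against usual care; it never uses that label. The simulated rates of a significant pooled result are illustrations: the document supports neither a combined HR of 2.5 nor exactly no effect alone, and the higher figures arise only if PA acts from day 0, contrary to the article's schedule.

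It would also be wrong to call combined against usual care the best-powered contrast. With HR 1.8 for e-Health, 1.2 for PA and 2.16 combined (PA from day 0), simulated power is about 85% to 89% for it and 92% for the pooled e-Health comparison.

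The reply does not remove the mismatch. The article itself lists the main comparisons and itself gives the interaction's purpose, and neither matches the hypothesis about usual care. This is a disagreement between stated hypothesis and stated analyses, not a detail left for later.

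**Conclusion.** The point holds in a limited form and should be corrected before analysis. The hypothesis that stepped care beats usual care has no stated contrast, although the randomised arms and a standard interaction model would supply one. This follows from the text alone and needs no numerical assumption.

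The pooled comparisons are valid averages over the other factor. Given the reinforcement the authors expect, they do not show what either intervention does alone. If each alone has HR 1.0 and the combination 1.8 to 2.5, the pooled e-Health HR is about 1.2 to 1.35 and significant in about 20% to 38% of trials with PA starting at six weeks. That range rests on the assumed HRs, exponential times and a 120-day control median. The direction depends only on a positive interaction.

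**What to change.** - Prespecify combined (e-Health and PA) against usual care, from the four-group Cox model (both main effects and their interaction), as the test of the stepped-care hypothesis, and give it a place in the testing order.
- From the same model, report e-Health only and PA only against usual care with confidence intervals as supporting estimates. Base any statement about one intervention without the other on these.
- Describe the pooled comparisons as average effects over the other factor.

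**Cost.** No new data or participants are needed. One comparison is added, so multiplicity must be addressed, and it uses half the participants. Its power depends on the true combined effect: roughly 50% to 70% at HR 1.8, depending on the event share, and about 100% at 3.24. The later start of PA reduces it: with no effect of either alone and a combined HR of 2.5 acting only from six weeks, the average HR against usual care is about 2.0 and power about 79%. The single-intervention contrasts also use two arms each and are similarly imprecise, which is why they are proposed as estimates with intervals and not as further tests.
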